
### Randomization and stratification

Screened and eligible patients will be allocated in a strictly concealed way by 2:1 randomization (intervention arm A vs. control arm B) block with variable block lengths randomization. During the randomization process stratification will be performed according to the following binary stratification variables:

fit for mFOLFOXIRI vs. mFOLFOX/CAPOX vs. 80%-mFOLFOX/CAPOXECOG 0 vs. ECOG 1–2left-sided primary vs. right-sided primary tumor (left-sided: splenic flexure and distal, right-sided: caecum to transverse colon)

Due to the nature of the intervention, blinding is not possible. However, given that the intervention in this trial are well established chemotherapy regimens, a center-driven bias caused by differing expertise appears highly unlikely and will not be compensated for.

### Primary endpoint

Disease-free survival (DFS) – defined as no surgery, no resection, incomplete resection, disease recurrence (new metastases or local relapse) and death from any cause from the time of randomization. In case of no surgery, no resection, or incomplete resection (defined as R2 resection = macroscopic tumor rest), the timepoint of the respective event will be set to two weeks after randomization to avoid time-bias in favor of the experimental/neoadjuvant therapy arm.

### Secondary endpoints

#### Efficacy

Overall survival (OS)Tumor regression by Dworak score

#### Safety

Type, incidence, severity, and causal relationship to active chemotherapy of non-serious adverse events and serious adverse events (severity evaluated according to CTCAE version 5.0)For surgical procedures the following assessments will be conducted: frequencies of infections, re-surgeries, anastomotic leaks. Further: days in hospital after resection, TNM-staging of resected specimen, R0/R1 resection rates, complication scores (Clavien-Dindo classification)

### Quality of life

Quality of life (QoL) as assessed with the QoL questionnaire EQ-5D-5L

### Exploratory endpoints

DFS, OS and Safety according to circulating tumor DNA at baseline (ctDNA positive vs. negative).DFS, OS and Safety according to molecular subgroupsDocumentation of post-study treatment anti-cancer therapies and their efficacy

### Experimental intervention

The study drug interventions to be used in arm A of this trial are mFOLFOX-6 or CAPOX or mFOLFOXIRI. A guidance is outlined in Table 1, however, at the discretion of the investigator, site specific modifications are permitted, e.g., additional 5-FU bolus, parallel leucovorin and oxaliplatin administration or variation of the infusion rates.

**Table 1 Tab1:** Trial medication (guidance for administration)

Drug	Dose/Potency	Duration of administration***	Route of Administration	Day(s) of application
*mFOLFOX-6 **regimen*:				
Oxaliplatin Leucovorin 5-FU*	85 mg/m² 400 mg/m² 400 mg/m^2^ bolus** 2400 mg/m²	2 h 0.5–2 h 2–5 min 46 h	IV Infusion IV Infusion IV Infusion IV Infusion	All at d1 of each 14- days cycle
*CAPOX **regimen*:				
Oxaliplatin Capecitabin	130 mg/m² 1000 mg/m²	~ 3 h Swallow twice daily	IV Infusion *Oral*	d1 d1-d14 of each 21-days cycle
*mFOLFOXIRI **regimen*:				
Oxaliplatin Irinotecan Leucovorin 5-FU*	85 mg/m² 150 mg/m^2^ 400 mg/m² 2400 mg/m²	2 h 90 min 0.5–2 h 46 h	IV Infusion IV Infusion IV Infusion IV Infusion	All at d1 of each 14-days cycle

(FOLFOX/FOLFOXIRI are given every 2 weeks as standard, CAPOX is given every 3 weeks as standard. CAPOX and FOLFOX may also start with 80% dosage of the indicated 100% dose level

* in DPD mutation carriers with a CPIC activity score of 1.0-1.5, 5-FU dosage should be reduced by 50%

** additional 400 mg/m2 bolus is permitted but not mandatory

*** infusion rates of chemotherapeutical components represent recommendations but might be modified according to local standards)

Given that fluoropyrimidines and oxaliplatin were used in the FOXTROT trial, their rationale in an extended preoperative treatment sequence appears reasonable. Further support of the use of these regimens (FOLFOX/CAPOX) is found in the neoadjuvant treatment strategies established in rectal cancer [7, 11]. Unlike FOLFOX/CAPOX, FOLFOXIRI was only evaluated in one relevant phase III trial- PRODIGE-23- as regimen addressing locally advanced rectal cancer. The main rationale for implementing FOLFOXIRI as neoadjuvant/preoperative therapy also in colon cancers may be that initial response presents an important component of the treatment goal in the context of high-risk tumors for R1 resection (as selected by this study protocol) [8, 9].

Trial interventions should be administered on day 1 of each cycle after all procedures/assessments have been completed. From the second cycle onwards, the chemotherapy may be administered up to 5 days after the scheduled day 1 of the respective cycles, due to administrative reasons with a minimum time span of 14/21 days (FOLFOX and FOLFOXIRI / CAPOX, respectively) between the cycles.

### Control intervention

The control arm will offer the current standard of care. For locally advanced colon and upper rectal cancer, standard of care is comprised of primary surgery followed by stage-guided adjuvant therapy [3, 4]. Surgical resection of the primary tumor should be performed as complete mesocolic excision to ensure a surgically radical approach and to minimize a potential bias. Non-complete mesocolic excisions will not represent a protocol deviation, but must be documented in the corresponding clinical report forms. The trial steering committee will assess the surgical resection strategies (open surgery, laparoscopic and robotic approaches) within the trial site selection process. Furthermore, central assessment of resected specimen will provide an additional control of surgical quality.

### Structured follow-up

There will be a structured follow-up for at least 60 months after randomization/treatment, for which several assessments will be necessary. After the structured follow-up, patients will be monitored for DFS and OS in the survival follow-up. The suggested follow-up regimen is shown in Table 2. A deviation by one month is accepted. In case of CT/MRI assessments at any time-point, the sonography of the abdomen might be cancelled at the discretion of the investigator.

**Table 2 Tab2:** Structured follow-up regimen

Investigation	Months in the follow-up (after surgery)							
	3	6	12	18	24	36	48	60
Patient history, anamnesis	x	x	x	x	x	x	x	x
Clinical examination	x	x	x	x	x	x	x	x
CEA assessment	x	x	x	x	x	x	x	x
CT (thorax/abdomen/pelvis)					x			
Abdominal ultrasound		x	x	x	x	x	x	x
Colonoscopy			x					

### Statistical analyses

#### Primary analysis

The null hypothesis to be tested in confirmatory analysis states that the hazard ratio for DFS comparing intervention versus control equals 1. This hypothesis will be tested by means of piecewise exponential model, by dividing the maximum follow-up time in 2 strata (0–2 years, 2–8 years), assuming the hazard is approximately equal in each time interval. This regression will be adjusted for the strata for randomization mentioned above. The two-sided significance level is set to 0.05. The primary analysis will be conducted based on the full analysis set which is defined as the intention to treat population. In a survival analysis setting, missing values are treated as non-informative censoring values so there is no need for imputation. 

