### Sample size

Based on the best available evidence described above [9, 10], 2-year DFS rate is 70% in the straight to surgery group and we hypothesize that DFS rate will be 78% in the neoadjuvant treatment followed by surgery group. To demonstrate an increase of 8% points in 2-year DFS rate (hazard ratio = 0.696), it is required to observe 271 DFS events, with the recruitment of 714 (476:238 per arm) patients with an allocation ratio of 2:1 (experimental vs. standard). These calculations assume that the DFS time follows a piecewise exponential distribution with two strata within the maximum follow up time ([0–2] years [2–8], years). For the first stratum, we assume that DFS rate will be 70% after 2 years in the control group. For the second stratum, we expect a level-off effect to a plateau of 60% DFS rate after 8 years. The sample size was calculated with 2-sided 5% level of significance, 80% power, with 5-year recruitment and 5-year follow-up periods and 5% drop-out in the first two years. The event rate in the straight to surgery group will be monitored annually by the independent data monitoring and ethics committee to ensure the baseline assumptions are appropriate. An interim analysis for efficacy will not be conducted. Given that an inferiority is unlikely with the background of TNT concepts in rectal cancer and previous trials and the increased sample size would impact on the feasibility of recruitment, interim analyses will solely focus on safety.

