#### Secondary analyses

As a sensitivity analysis to the primary efficacy analysis, the same test will be repeated on the per-protocol population including all patients without major protocol violations. As another sensitivity analysis, the primary hypothesis will also be evaluated by computing the restricted mean survival at 5 years. Event probabilities of DFS will be estimated by Kaplan-Meier-Curves. The above analyses will be repeated for overall survival. The influence of treatments received after the period of intervention on DFS and OS will be assessed. Specific post-study treatments will be included in the piecewise exponential model as time-dependent explanatory variables. Longitudinal models will be fitted to examine the evolution over time of the two arms and to test potential differences between them. Circulating tumor DNA, tumor markers and molecular information as well as quality of life/ patient reported outcomes will be evaluated exploratory.

The intent-to-treat population includes all randomized patients. Treatment assignment is based on the randomized treatment (primary population). The ITT population is the primary population for the description of the patient and treatment characteristics and is used for the primary efficacy analysis. The per-protocol (PP) population will include all randomized patients fulfilling the inclusion and exclusion criteria and who received at least one cycle of active treatment with at least one documented structured follow-up visits (arm A) or with at least one documented follow-up visit (arm B). Treatment assignment is based on the treatment actually received. Patients with major protocol violations will be excluded.

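### The primary DFS model assumes one constant hazard over 0–2 years, but the endpoint rule stacks all no-surgery, no-resection and R2 events at week 2, so a model-based standard error is slightly too small

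*Protocol article*

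**What the plan says.** Protocol article, Primary analysis: DFS is tested with a piecewise exponential model that splits follow-up at 2 years (0–2 and 2–8 years), "assuming the hazard is approximately equal in each time interval", adjusted for the randomization strata. "The two-sided significance level is set to 0.05". Neither a variance estimator nor an earlier cut-point is mentioned.

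Protocol article, Primary endpoint: if there is no surgery, no resection or an R2 resection, "the timepoint of the respective event will be set to two weeks after randomization". The stated purpose is to prevent a timing bias in favour of the neoadjuvant arm. The rule applies to both arms. The expected share of such patients is not given.

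Protocol article, Sample size: the same two-piece shape is used for planning, with control DFS of 70% at 2 years and 60% at 8 years. No early cluster of events is mentioned there.

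**The concern.** The two specifications do not fit together. A constant hazard over 0–2 years spreads failures in proportion to time at risk. The endpoint rule instead puts a block of failures on a single day and leaves a lower hazard for the rest of the two years. This happens by design whenever such cases occur.

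The consequence is mainly in the variance. A patient who fails at week 2 has contributed almost no exposure, and the model treats that failure as if it came from the interval's average rate. The actual variability of the log hazard ratio is then larger than the model-based standard error suggests. The nominal 5% level is exceeded and the confidence interval is a little too narrow. This is the trial's only confirmatory test, so even a modest excess matters if the result is borderline.

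**Working it through.** **Reproducing the plan's figure.** The inputs are "To demonstrate an increase of 8% points in 2-year DFS rate (hazard ratio = 0.696"), 2:1 allocation, two-sided 5% and 80% power. Schoenfeld's formula is D = (1.960 + 0.842)² / [(2/3)(1/3)(ln HR)²].
- With HR = 0.696: 7.849 / (0.2222 × 0.1313) = 268.9, so 269 events.
- With the unrounded HR = ln 0.78 / ln 0.70 = 0.6966: 7.849 / (0.2222 × 0.1307) = 270.2, so 271 events.

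This matches "it is required to observe 271 DFS events". At 271 events the standard error of the log hazard ratio is 1/√(271 × 2/9) = 0.129.

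**Inputs for the check** (Sample size section unless noted):
- 476:238 patients.
- Control hazard after 2 years: ln(0.70/0.60)/6 = 0.0257 per year.
- Follow-up uniform over 5–10 years (5 years of recruitment plus 5 years of follow-up).
- 5% drop-out in years 0–2.
- Share q of patients dated at week 2: assumed, because the article does not give it. These patients are counted within the 30% of control failures by 2 years.

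To keep 2-year control DFS at 70%, the remaining 0–2 year hazard is a(q) = ln[(1 − q)/0.70]/2. This is 0.178 at q = 0, 0.168 at 2%, 0.153 at 5% and 0.126 at 10%. The larger the spike, the lower the hazard that follows it.

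**Large-sample level under the null.** For each patient take r = (d₁ − λ₁e₁) + (d₂ − λ₂e₂), where d is the event indicator, e the exposure and λ the fitted hazard in each interval. The ratio of true to model standard error is k = √(mean r² / mean d), and the actual level is 2[1 − Φ(1.960/k)]. For q = 5%, k = 1.0214, 1.960/k = 1.919 and the level is 5.5%.

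**Simulation under the null.** 60,000 trials per share, Monte Carlo error √(0.05 × 0.95/60,000) = 0.09 percentage points:

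| q | k | Large-sample level | Two-piece SD/SE | Two-piece level | SD/SE with extra cut at week 4 | Level with extra cut |
|---|---|---|---|---|---|---|
| 0% | 1.000 | 5.0% | 1.005 | 5.05% | 1.005 | 5.04% |
| 2% | 1.009 | 5.2% | 1.010 | 5.10% | 1.002 | 4.93% |
| 5% | 1.021 | 5.5% | 1.026 | 5.42% | 1.005 | 4.92% |
| 10% | 1.044 | 6.05% | 1.046 | 5.99% | 1.002 | 4.95% |

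The level is nominal without a spike, rises with q and returns to nominal when the spike has its own interval. A robust variance in the two-piece model gives 5.1–5.2% at q = 2–10%.

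**Effect on the estimate.** Under the null with equal shares in both arms, the mean hazard ratio is 1.00. Under proportional hazards that include the early mass (true HR 0.697; 6,000 trials each), with q the control-arm share:

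| q | Two-piece HR | HR with extra cut |
|---|---|---|
| 2% | 0.695 | 0.697 |
| 5% | 0.694 | 0.698 |
| 10% | 0.688 | 0.697 |

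The shift from the true value is about 0.3%, 0.4% and 1.3%. The largest shift is about 0.013 on the log scale, one tenth of the 0.129 standard error.

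**Is the dating rule to blame?** The same events were placed at assumed actual times (week 16 in arm A, week 4 in arm B; 12,000 null trials each). The two-piece level is then 5.5% and 5.9% at q = 5% and 10%, about the same as before. The null hazard ratio drifts to 0.996 and 0.991, in favour of arm A.

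The simulations did not include the stratification covariates.

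**The case against.** **The size depends on an unstated share.** This stands. Patients must be intended for curative surgery, have no clear distant metastases and not be obstructed, and only R2 resections count as incomplete. A low share is plausible, and at 2% or less the excess is about 0.2 points at most. A share of 10% would be one third of the 30% control failures expected by 2 years.

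**The variance estimator is not fixed in the article.** This also stands in part. The excess arises only with a model-based variance, and a robust one may be specified in an analysis plan that is not shown. What the article does fix is the single cut at 2 years beside the week-2 rule, and those two conflict.

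**Other planned analyses avoid the assumption.** Restricted mean survival at 5 years and Kaplan-Meier curves do not use the two-piece hazard. They would help to expose a model-driven result, but neither is the confirmatory test.

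**Stronger readings that a reader might infer:**
- *The treatment effect is overstated.* Not in general. There is no bias under the null, and the shift under proportional hazards is small. With more early failures in arm A (8% against 4%), the two-piece HR is 0.835 against 0.838 with the early cut, a negligible difference.
- *The week-2 rule is the fault and should go.* Dating the events at assumed actual times leaves the level almost unchanged and adds the drift that the rule is meant to prevent.
- *The same defect affects overall survival*, because "The above analyses will be repeated for overall survival". The week-2 rule is part of the DFS definition only and creates no spike in OS.
- *The model must be replaced by Cox.* An early cut or a robust variance is enough.

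**Conclusion.** The concern holds as a modest point about the calibration of the primary test. The article's endpoint rule contradicts the constant-hazard assumption for 0–2 years. With a model-based variance, the standard error is about 1–5% too small, and the actual two-sided level is about 5.1–5.2%, 5.4–5.5% and 6.0% at week-2 shares of 2%, 5% and 10%. The direction is clear. The size rests on the assumed share, on the Sample size section's DFS rates and follow-up, and on a model-based variance, and the calculation leaves out the stratification covariates. The results do not support a claim of material bias in the hazard ratio or any criticism of the week-2 rule itself. Because the test is confirmatory and the correction is nearly free, it should be made.

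**What to change.** Keep the week-2 dating rule. In the protocol and analysis plan, make one of these changes to the primary analysis:
1. add a cut-point at about one month, giving intervals of 0–1 month, 1 month–2 years and beyond 2 years; or
2. keep the two intervals and specify a robust (sandwich) variance; or
3. use a Cox model adjusted for or stratified by the randomization strata. Tie handling must then be stated, since all week-2 events share one time: about 36 at a 5% share of 714 patients (0.05 × 714 = 35.7). This option agrees with the planned 271 events, which the Schoenfeld formula reproduces.

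Keep the two-piece model as a sensitivity analysis.

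The cost is wording, one extra nuisance parameter for option 1, and at most a very slightly wider confidence interval. In the simulations under proportional hazards, the extra cut lowered the rejection rate by 0.3, 0.9 and 1.7 percentage points at shares of 2%, 5% and 10%. Part of that is the excess level being given back. No additional patients or data are needed.

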**Methods and design:**

Open-label, randomized, controlled, multicenter, phase III study with two parallel arms. Patients with locally advanced colon or upper rectal cancer staged cT3-4 and/or cN+ are randomized in a 2:1 fashion (favoring preoperative therapy) to investigate the efficacy, patient reported quality of life, and safety of preoperative therapy followed by surgery (Arm A) versus direct surgery followed by non-study specific stage-guided adjuvant therapy (Arm B). Stratification during randomization will be performed according to the following parameters: Fit for mFOLFOXIRI vs. mFOLFOX/CAPOX vs. 80%-mFOLFOX/CAPOX, ECOG 0 vs. ECOG 1-2, and left-sided primary vs. right-sided primary tumor. Only patients with confirmed mismatch-repair proficient and/or microsatellite stable tumor can be included.

Preoperative treatment in Arm A is performed for a maximum of 6 biweekly cycles of FOLFOX/FOLFOXIRI or for a maximum of 4 triweekly cycles CAPOX (i.e., appr. 12 weeks). Patients in both arms should undergo quality-controlled surgery of the primary tumor, performed as complete mesocolic excision.

Patients will be followed up with regard to relapse, survival and if applicable subsequent anti-cancer treatments until death or for at least 5 years after randomization, whichever date is earlier.

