## Background

Colorectal cancer is the third most common cancer diagnosed in women and men, it was the fourth-leading cause of cancer death in both men and women younger than 50 years in the late-1990s but is now first in men and second in women [1]. In Germany, approximately 55,000 to 60,000 new cases are diagnosed annually [2]. Colon cancer accounts for two thirds of all colorectal cancer cases.

In patients with colon or upper rectal cancer, irrespective of the assumed T/N-stage, the standard of care in the absence of metastases is surgery, which is followed by stage-guided adjuvant therapy and/or structured follow-up [3]. Adjuvant therapy is clearly indicated in UICC stage III patients (nodal positive) and also recommended in some patients with UICC II (T3-4, N0 tumors) with respective risk criteria (T4 tumors, emergency surgery, perforation, insufficient lymph node harvest etc.) [3, 4].

The strategy of neoadjuvant or perioperative systemic therapy represents an emerging concept in solid tumors and is already a standard of care in some gastrointestinal cancers such as advanced gastric and esophageal junction cancer, and notably in advanced lower rectal cancer [5–8]. Concepts addressing the lower rectal cancer, biologically similar to colon cancer, include total neoadjuvant therapy (TNT) as a new standard of care [7, 8]. Potential benefits of neoadjuvant therapy for patients, contributing to improved long-term outcome, include:

Population effect: nearly 100% exposition to chemotherapy vs. only those patients that are fit enough to receive chemotherapy after resection.Earlier treatment of micrometastases.Downstaging of the primary tumor, enabling easier resections.Pre-habilitation before radical surgery.

In locally advanced colon cancer, two phase III trials have investigated perioperative treatment with 6/12 weeks of systemic therapy before surgery, in both cases doublet therapy with FOLFOX/CAPOX. The FOXTROT trial was first presented at the 2019 ASCO congress with lacking anticipated event rates and was consecutively rated “negative” with a borderline-significant *p*-value. This was despite exactly hitting the predefined effect size. In summary, FOXTROT suggested that perioperative therapy in colon cancer is safe and might be beneficial in terms of disease-free survival and overall survival [9].

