### Inclusion criteria

Participants are eligible to be included in the trial only if all of the following criteria apply at time of enrollment:

Patient’s signed informed consent.Patient’s age ≥ 18 years at the time of signing the informed consent.Histologically confirmed adenocarcinoma of the colon or upper rectum.Confirmed mismatch-repair proficient and/or microsatellite stable tumor. Both immunohistochemistry and PCR can be used for diagnosis.Intent for curative surgery.Predicted (clinical) T3 or T4 stage and or nodal positivity (N+) assessed by the local study team based on computed tomography and/or magnetic resonance imaging of the abdomen and pelvis. The imaging criteria were adjusted to achieve a low false positive rate.T3-4 defined as unequivocal signs of invasion of surrounding tissue structures or organs N+ defined as regional (within drainage territory of the primary site) lymph node(s) without fat hilus or occupying calcifications enlarged to a short/long axis diameter of ≥1/1.5 cm (for ileocecal region ≥ 1.3/1.8 cm)Absence of clear distant metastases assessed by the investigator based on respective routine evaluations within 6 weeks prior to inclusion into the trial (Preferred: computed tomography of thorax and abdomen. Alternatively, magnetic resonance images, FDG-PET, sonography and x-rays might be used for assessment).Absence of significant active wound healing including severe chronic non-healing wounds, ulcerous lesions or untreated bone fracture.ECOG performance status 0-2.Adequate bone marrow, hepatic and renal organ function, defined by the following laboratory test results:Absolute neutrophil count ≥ 1.5 x 109/L (1,500/µL).Hemoglobin ≥ 80 g/L (8 g/dL) with or without transfusion.Platelet count ≥ 100 x109/L (100,000/µL) without transfusion.Total serum bilirubin of ≤ 1.5 x upper limit of normal (ULN).Aspartate aminotransferase (AST) ≤ 3.0 × ULN.Calculated glomerular filtration rate (GFR) according to Cockcroft-Gault formula or according to MDRD ≥ 50 mL/min or serum creatinine ≤ 1.5 x ULN.Patients without anticoagulation need to present with an INR < 1.5 x ULN and PTT < 1.5 x ULN. Patient with prophylactic or therapeutic anticoagulation are allowed into the trial.Proficient fluorouracil metabolism as defined:Prior treatment with 5-FU or capecitabine without unusual toxicity or,If tested, normal DPD deficiency test according to the standard of the study site, orIf tested, in patients with DPD deficiency test with a CPIC activity score of 1.0-1.5 fluoropyrimidine dosage should be reduced by 50% and patients are allowed into the trial.For women of childbearing potential (WOCBP): negative pregnancy test within 7 days before treatment initiation and agreement to remain abstinent (refrain from heterosexual intercourse) or use contraceptive methods with a failure rate of < 1% per year during the treatment period and for at least 6 months after the last dose of study treatment.

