Earlier treatment (6–8 weeks) of distant micrometastases.Increased exposition to chemotherapy as appr. 20% of initially operated patients are not eligible for post-operative chemotherapy (complications, patient preferences) [9].Reduction in tumor size, easier resection and likely less complications [9].

On the other hand, it can be argued that pre-operative staging with CT-scans will result in a certain fraction of patients with “over-staging” that consecutively receives chemotherapy in the experimental arm despite a “real” TNM stage that would not qualify for adjuvant systemic therapy if upfront assessed after surgery. Therefore, PROTECTOR / FIRE‑10 will implement control systems to overlook and reduce the proportion of “over-staged” patients:

Radiology workshop to provide quality control of CT assessments. These will be organized virtually and refer to standard cases and demonstrate criteria of selection of patient for the trial.Reassessment of TNM-stage in the control arm after 50, 100 and 150 primarily resected patients and consecutively the option to react to the frequency of over-staged patients - if necessary.

In conclusion, the PROTECTOR / FIRE‑10 trial is designed to provide evidence whether patients – and if so, which patients – will benefit from a preoperative systemic therapy before surgical resection of locally advanced colon cancer including the upper third of the rectum.

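### The primary DFS model adjusts only for the randomisation strata and omits baseline clinical T and N stage: the test stays valid, but a modest, assumption-dependent amount of power is given up

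*Protocol article*

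**What the plan says.** **Model.** The Primary analysis section of the protocol article tests DFS with a piecewise exponential regression on two intervals (0–2 and 2–8 years) and names its covariates: "This regression will be adjusted for the strata for randomization mentioned above".

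**Strata.** The abstract's Methods and design paragraph lists them as "Fit for mFOLFOXIRI vs. mFOLFOX/CAPOX vs. 80%-mFOLFOX/CAPOX", then "ECOG 0 vs. ECOG 1-2, and left-sided primary vs. right-sided primary tumor". The section on randomisation and stratification gives the same three. Stage is not among them, and no other section names it as a covariate.

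**Stage at entry.** The inclusion criteria require "Predicted (clinical) T3 or T4 stage and or nodal positivity (N+) assessed by the local study team", read from CT and/or MRI. T3-4 is given one joint imaging definition; N+ has its own size criteria.

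**Stage as a risk marker.** The Background says "Adjuvant therapy is clearly indicated in UICC stage III patients (nodal positive"), and that some stage II patients are also treated, "with respective risk criteria (T4 tumors, emergency surgery, perforation, insufficient lymph node harvest etc".

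**Limits of imaging stage.** The Discussion accepts that "pre-operative staging with CT-scans will result in a certain fraction of patients with “over-staging" and plans to reassess TNM stage after 50, 100 and 150 resected control patients.

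**The concern.** Stage is determined before allocation in both arms and cannot be affected by treatment. The article itself expects the T/N mix to matter for the event count: the Background lists surveillance of stage in the control arm as a design feature for that reason. Yet neither the randomisation nor the model takes account of stage differences between arms.

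In a hazard model, leaving out a prognostic covariate pulls the estimated treatment effect slightly towards 1 and loses some power. It also leaves chance imbalance in that covariate as noise in the estimate. Pre-specified adjustment recovers part of this without inflating the type I error. Adjustment chosen after the data are seen would be open to the charge of selection, so the time to decide is now.

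**Working it through.** **Inputs from the article (Sample size section).** "2-year DFS rate is 70% in the straight to surgery group", 78% in the experimental arm, hazard ratio 0.696, control plateau 60% at 8 years, 271 events, 714 patients (476:238), two-sided 5%, 80% power, 5 years' recruitment plus 5 years' follow-up, 5% drop-out in the first two years.

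**Step 1: reproduce the plan's figures.**
- Hazard ratio: ln 0.78 / ln 0.70 = 0.6966.
- Events (Schoenfeld, 2:1): (1.960 + 0.842)² / [(1/3)(2/3)(ln 0.6966)²] = 7.849 / (0.2222 × 0.1307) ≈ 270.2, rounded up to 271. This matches.
- Patients: 271 / 0.40 / 0.95 = 713.2, so 714. This also matches, but it applies the control arm's 8-year event rate of 40% to both arms.

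**Step 2: starting power at 714 patients.** Control hazards are −ln(0.70)/2 = 0.178 per year up to year 2 and ln(0.70/0.60)/6 = 0.0257 per year afterwards. With hazard ratio 0.696 in both intervals, uniform accrual and the stated drop-out, expected events are 135.0 + 90.5 = 225.5, or about 226.
- Standard error of the log hazard ratio: √(1/135.0 + 1/90.5) = 0.136.
- Wald power: Φ(0.362/0.136 − 1.96) ≈ 76%. Schoenfeld gives 72.8%, and simulation about 75%.

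The simulations below therefore start from about 75%.

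**Step 3: effect of adding cT4 and cN+.** The article gives no prognostic hazard ratios or prevalences, so these are assumed: 30% cT4 and 50% cN+. Baseline hazards were recalibrated in each scenario so that overall DFS stays at 70% and 60% (control, years 2 and 8) and 78% (experimental, year 2). There were 12,000 trials per row, each analysed with the two-piece exponential model with and without the two terms.

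| Assumed HR, cT4 / cN+ | Power without | Power with | Gain (points) |
|---|---|---|---|
| 1.3 / 1.3 | 75.3% | 75.8% | 0.5 |
| 1.5 / 1.5 | 74.1% | 75.4% | 1.3 |
| 2.0 / 1.5 | 74.9% | 77.8% | 2.9 |
| 2.0 / 2.0 | 74.7% | 78.3% | 3.6 |
| 2.5 / 2.0 | 75.3% | 80.1% | 4.8 |

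Under no treatment effect (2.0 / 1.5), rejection rates were 5.0% without and 5.1% with the terms. A separate set at 60% cN+ (2,000 trials per scenario) agreed: 75.9 to 77.0%, 74.7 to 77.0% and 74.2 to 79.0% for 1.5/1.5, 2.0/1.5 and 2.5/2.0.

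The table's comparator has no strata terms, whereas the plan's model has them. A direct comparison of strata-only with strata plus cT/cN gave the same range, about 0.4 to 5 points.

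**Step 4: misclassified imaging stage.** If the hazard ratios belong to true stage and imaging is right 80% of the time (assumed), the gain falls to about 1 point. At 70% sensitivity and specificity (also assumed), gains for 1.5/1.5, 2.0/1.5 and 2.5/2.0 were −0.1, +0.1 and +0.8 points, which for the first two is simulation noise around zero.

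**Step 5: chance imbalance.** For a 30% factor, the standard error of the between-arm difference is √[0.3 × 0.7 × (1/476 + 1/238)] = 3.6 points. At a cT4 hazard ratio of 2.0, one such standard error moves the log hazard ratio by about 0.036 × 0.693 = 0.025, against its standard error of 0.136.

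**The case against.** The strongest reply is that nothing here is wrong. Adjusting for the stratification factors is conventional, agrees with the randomisation scheme and gives a valid test. A statistical analysis plan, not shown, might add covariates. The Background passages on nodal disease and T4 concern adjuvant decisions, which follow pathological stage; they do not show that imaging stage predicts DFS. The article expects over-staging, gives no prognostic hazard ratio, and defines T3-4 jointly, so a usable cT4 variable may not be on the baseline form.

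Most of this stands, and it limits the point to lost efficiency of uncertain size. It does not remove the point: the article states the covariate set of its confirmatory model, so an analysis plan that follows it would leave stage out, and staging on imaging happens before allocation in both arms.

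A reader might infer three stronger claims that the documents do not support:
- **That omitting stage biases the comparison or leaves imbalance uncontrolled.** Randomisation handles this on average, and the 5% test already allows for chance imbalance; step 5 shows that a typical imbalance is small beside the sampling error.
- **That this omission explains power below 80%.** That shortfall comes from the Sample size section's use of the control event rate for both arms. If 271 events were reached, power would be 80.3%.
- **That adjustment restores 80%.** Only the most favourable row of the table gets there, and only with error-free staging.

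**Conclusion.** The point holds as a modest efficiency improvement to a stated method. The primary model leaves out two baseline characteristics that are assessed before randomisation. Adding them would gain roughly 0 to 5 power points for prognostic hazard ratios of 1.3 to 2.5, and about 1 point or less if imaging stage is considerably misclassified, with no inflation of the type I error. These figures rest on assumed hazard ratios, prevalences (30% cT4, 50 to 60% cN+) and imaging accuracy, none of which the article gives. They apply to 714 patients over the stated 5 + 5 years. The gap between about 226 and 271 expected events needs its own answer.

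**What to change.** In the Primary analysis section and the analysis plan, pre-specify that the DFS regression is adjusted for the randomisation strata plus cN+ (yes/no) and cT4 (yes/no), both as read on imaging before randomisation. State that pathological stage is not to be used, because preoperative therapy can alter it in Arm A. Report the strata-only model as a sensitivity analysis.

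The cost is a sentence or two and two extra model parameters. One practical step is needed: since the inclusion criteria define T3-4 jointly, confirm that the baseline form records cT4 separately from cT3, or take it from the baseline imaging report, including for patients already enrolled. Make the change before outcome data by arm are seen.
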